**Fig. 2 Fig2:**
[figure not shown]
Title: Map of study areas. Legend: Study districts including, the intervention (orange) and control areas (teal) in the Central Region in Cameroon (**A**) and in the Worodougou Region in Côte d’Ivoire (**B**), are shown. Selected health facilities are represented by the black dots. Study regions within each country are shown in the red bounded areas in the inset maps

### Cameroon

Soa and Mbankomo are peri-urban areas located on the north-eastern and south-western periphery of Yaoundé, respectively (Fig. 2). Both areas have an estimated population density of 1,235 people per squared km and 15% of the population is under 5 years of age. In total, there are 39 health facilities in Soa, 12 of which are public and 28 have active CHWs. Of the 39 facilities, 20 administer EPI services and are eligible for SP administration as part of the expanded PMC programme. In Mbankomo, there are 32 health facilities, of which 4 are public and 10 have active CHWs. Of the 32 facilities, 19 administer EPI services and are eligible for SP administration as part of the standard of care PMC programme. Malaria incidence in both Soa and Mbankomo was 597 cases per 1000 children under 5 in 2020 [12]. Malaria transmission is typically highest during the two rainy seasons, from March to June and from October to November.

### Côte d’Ivoire

Séguéla and Kani are rural areas located approximately 500 km northwest of the capital city, Abidjan (Fig. 2). The estimated population density is 45.98 people per squared km (2021) and 18% of the population is under 5 years of age. In total, there are 42 health facilities in Séguéla, all of which are public and 33 of these have active CHWs. Of the 42 facilities, 41 administer EPI services and thus are eligible for SP administration as part of the expanded PMC programme. In Kani, there are 8 health facilities, all of which are public and have active CHWs. Of the 8 facilities, all administer EPI services and thus would be eligible for SP administration if any doses were given as part of a standard of care PMC programme. According to the NMP, malaria incidence in both Séguéla and Kani was 572 cases per 1000 children under 5 in 2020 with the peak typically from April to July during the rainy season.

### Study design

All health facilities providing EPI services in selected study sites and corresponding catchment populations will be eligible for inclusion and constitute the primary sampling unit for this evaluation. Health facilities will be randomly selected for inclusion (Fig. 3). All non-EPI/PMC facilities within the selected EPI catchment areas, will be included in the passive cohort data collection, described below (Table 1). In the selected EPI facility catchment areas, several study activities will be conducted: (i) a census to enumerate all households, primary caregivers and children under 36 to characterize the population eligible to receive PMC (0–24 months) as well as when they age out of the intervention (25–36 months), (ii) a passive cohort at health facilities to monitor clinical episodes of malaria and anaemia as well as receipt of EPI vaccinations and PMC in children under 36 months, and (iii) to monitor malaria and anaemia in a subgroup of participating children in an active cohort over an 18-month period. The same procedures will be employed in both intervention and control areas in Cameroon and Côte d’Ivoire.

**Table 1 Tab1:** Eligibility criteria for each study component in the PMC impact evaluation study

	Inclusion Criteria	Exclusion Criteria
**Health Facilities**	- Located within the target study sites - Administer EPI/PMC services	- Located outside of the target study area
**Census - Household**	- Located within the catchment area of selected health facilities - Head of household provides consent	- Located outside of the selected health facility catchment area - Head of household not present or refuses participation
**Passive Cohort - Child**	- Regularly resides in households included in the census - Age 36 months or less at time of census - Primary caregiver provides informed consent	- Head of household refused participation in the census - Primary caregiver not present or refuses participation - Not expected to reside in the selected household for the study duration - Age greater than 36 months of age at recruitment visit
**Active Cohort - Child**	- Recruited into the passive cohort - Aged between 6–9 months in Cameroon and 10 weeks and 6 months in Côte d’Ivoire at point of recruitment - Primary caregiver provides informed consent	- Head of household/caregiver refused participation in the census and/or passive cohort - Not within the identified age category at the point of recruitment - Primary caregiver not present or refuses participation

**Fig. 3 Fig3:**
[figure not shown]
Title: Study population Legend: Overview of the structure of the study design including sample size of facilities and children for each component and how many were excluded at the design stage

### Census

A census of the population will be conducted in each selected EPI catchment area to create a sampling frame that will support both the passive and active cohorts. Specifically, all households in the selected EPI catchment areas will be approached for inclusion (Table 1). Written, informed consent will be obtained from the head of household for participation in the study. Information recorded will include the GPS coordinates of the household, information on house construction, socioeconomic position, use of vector control interventions, healthcare-seeking behaviours, and the number of people residing in the household composition according to age groups. (i) ≤ 3 years, (ii) > 3 to < 5 years, (iii) ≥ 5 years to < 21 years, and (iv) ≥ to 21 years. Each household will be assigned a unique, non-identifiable number that will be included on study documentation and written on household’s doorframe for future localisation.

The census will take place prior to the PMC implementation and will be updated at 3-monthly intervals throughout the 18-month study period. During the census update, any births, deaths, or immigration and emigration will be recorded. The same study procedures during the initial census visit will be followed for new recruits. For any participants that have died since the previous visit, a brief questionnaire will be administered where possible to obtain information on the date of death, whether it was in a health facility or at home, and broad categories of the potential cause of death (i.e., traffic accident, health episode etc.) and other relevant information. Due to the sensitive nature of this data and difficulty in obtaining the precise cause of death in the community, verbal autopsies will not be conducted and any deaths without a confirmed cause of death will be excluded from analysis.

### Passive cohort

All children up to 36 months of age residing in enumerated households during the census will be eligible for inclusion in the passive cohort and enrolled upon provision of written informed consent from their primary caregiver (Table 1). Enrolled children will be passively monitored to record both EPI vaccinations and PMC visits as well as clinical visits for malaria and anaemia to the health facility and/or CHWs over the 18-month study period. Older children (24 to 36 months at baseline) are not eligible to receive the intervention but will be enrolled in this study activity for two reasons: first, the older children will serve as an internal control as it is assumed that they will experience a similar malaria transmission intensity but will not receive the intervention and, secondly, as children will be followed for 18 months information will be available on children who age-out of eligibility to assess any impact beyond when children are eligible to receive PMC. Children will not be censored according to age.

During the passive cohort recruitment, trained fieldworkers will record basic demographic information about the child, recent malaria cases, amongst other information. An anonymous and unique QR code with the participant ID linked will be attached to each child’s health and vaccination record books. This QR code will be used to identify children participating in the study when they interact with the health system and facilitate linking the data generated by the routine system on EPI, PMC or clinical visit, which are stored in separate registers, with the research activities. During recruitment, the national health ID number assigned to each child and written in the health and/or vaccination record books will be recorded. The names of children and primary caregivers will also be recorded to provide a means to verify that children present match ID numbers. This also serves as a back-up method to link health information data that is routinely collected in different registers. Caregivers will be encouraged to take children to the participating facilities or CHWs to receive EPI vaccinations or PMC or for any illnesses.

Study staff will be present during the scheduled EPI visits to record when children received each dose of PMC. This may occur at health facilities or during active campaigns initiated by the health facility staff where vaccinations, including the newly introduced RTS, S vaccine where present, Vitamin A or SP is distributed. Data collected will include the child’s ID number, the date, location, and which health interventions were administered at that contact point. Where CHWs administer some of the SP or Vitamin A doses, they will record the data for the relevant contact point. The study staff will also collect, information on all clinical malaria and anaemia episodes throughout the 18-month study period. When a child participating in the passive cohort (i.e., has a QR code in their record book or the caregiver makes their participation known and confirmed through looking up their name) visits a study health facility or CHW, information about their visit will be recorded including date, diagnosis and treatment received and whether a referral was made. For children receiving inpatient treatment for anaemia or malaria, additional information including clinical symptoms and details of any complications, treatments received, the outcome, and date of discharge will be collected. Data will also be collected on any children who die in hospital during the study period. All data will be obtained from the clinical registries and confirmed by the facility staff.

Finally, to ensure that results are interpreted within the context of the broader trends in malaria transmission and the incidence of anaemia, routine surveillance data for each health facility will be collected up to five years before the start of the evaluation untill the end of the study. Data will consist of monthly aggregated data per health facility per 12-monthly age-band for children under 5 years of age. Key variables to be collected include the number of attendees, number of uncomplicated and complicated malaria cases, the number of malaria deaths, the number of anaemia and severe anaemia cases.

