### Data analysis

The primary analysis will be based on intention to treat (ITT), including all children residing in the intervention area as the exposed group. All available data up to the time of censuring (e.g., loss to follow-up, withdrawal, death, or study completion), irrespective of whether the child received any, part, or all the intended PMC doses. An additional per-protocol analysis will be completed which includes children who received at least one dose, all doses, or specific doses of PMC. The period of protection provided by SP is up to one-month post treatment and thus will constitute the protective window of those receiving the intervention. Data for both countries will be combined for analysis as well as assessed separately to ensure context specific nuances are fully assessed.

Incidence rates for malaria and anaemia will be calculated using multivariable Poisson regression, difference-in-difference, and interrupted time-series models comparing intervention and control areas [14–16]. Incidence rates, rate differences, and rate ratios between intervention and control area will be calculated for the ITT and per-protocol analysis. Malaria incidence will be determined by the number of malaria cases confirmed by either RDT or microscopy identified in either the passive or active cohort. Person-time at risk for each study outcome will be calculated based on the date of recruitment into the study population until the date of censuring or study end. For children who leave the study prior to the end date, the date of exit will be the date where they moved, withdrew from the study, or died. If that date is not known, the midpoint between the date of last contact and the date the loss was detected will be used. Protective effectiveness will be calculated for the intervention period including the 18 months of follow-up for the periods where PMC doses differ, stratified by first and second year of life, as well as during the post-intervention period, starting at 24 or 18 months of age in Cameroon and Côte d’Ivoire, respectively, to estimate any potential rebound in malaria.

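### The rebound period is fixed by age alone, so in the passive or combined cohort it takes in children who never had access to the added doses, and the age limits given for Côte d'Ivoire do not agree

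*Protocol article*

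**What the plan says.** All references are to the protocol article.

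- **Study design** sets one pair of age bands: "population eligible to receive PMC (0–24 months) as well as when they age out of the intervention (25–36 months" months. It makes no distinction by country and adds "The same procedures will be employed in both intervention and control areas in Cameroon" and Côte d'Ivoire.
- **Passive cohort** enrols widely: "All children up to 36 months of age residing in enumerated households during the census will be eligible for inclusion in the passive cohort". It states "Older children (24 to 36 months at baseline) are not eligible to receive the intervention", gives as one reason for enrolling them that "the older children will serve as an internal control", and adds "Children will not be censored according to age". Follow-up is 18 months.
- **Census** places the baseline enumeration before PMC begins.
- **Data analysis** treats every child resident in the intervention area as exposed, counts person-time from recruitment and takes malaria cases from either cohort. It estimates protective effectiveness in a post-intervention period "starting at 24 or 18 months of age in Cameroon and Côte d’Ivoire, respectively, to estimate any potential rebound in malaria".
- **Active cohort** recruits at 6 to 9 months of age in Cameroon and at 10 weeks to 6 months in Côte d'Ivoire, partly so that children can be observed after their last possible dose.

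**The concern.** There are two linked problems.

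1. **The age limits do not agree for Côte d'Ivoire.** Take a child there aged 20 months at baseline. Study design puts this child in the eligible band. Data analysis puts the same child in the post-intervention period from the first day. The child is too young for the internal control group described under Passive cohort.

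2. **The rebound period is defined by attained age, not by earlier access to the intervention.** Rebound means a raised risk after protection ends, so it can occur only in children who had access to the doses that differ between areas. A child already past the cut-off when PMC starts had no such access. Under the stated rules that child still contributes time to the rebound rate throughout follow-up, and in the intervention area does so as exposed. Children of 24 to 36 months would then serve both as internal control and as exposed rebound person-time.

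The rebound estimate would be pulled towards no difference, and a programme could read that as evidence that ageing out of PMC carries no added risk.

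**Working it through.** The article gives no figure for the make-up of the rebound period, so there is none to reproduce. The check is a person-time count by baseline age.

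**Inputs from the article:** enrolment at 0 to 36 months; 18 months of follow-up; no age censoring; rebound start at c = 24 months (Cameroon) or c = 18 months (Côte d'Ivoire).

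**Assumptions:** baseline ages uniform over 0 to 36 months, PMC starting at baseline, no loss. Never eligible means aged c or more at baseline.

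**Formulas** (a = baseline age in months; units are arbitrary):
- Never eligible: (36 − c) × 18.
- Eligible at baseline: the integral of (a + 18 − c) over ages a below c for which this is positive.

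**Cameroon, c = 24**
- Never eligible: 12 × 18 = 216.
- Eligible: integral of (a − 6) from 6 to 24 = 18²/2 = 162.
- Share never eligible: 216/378 = 57%.
- Head count: of the children who reach 24 months in follow-up (baseline ages 6 to 36), 12/30 = 40%.

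**Côte d'Ivoire, c = 18**
- Never eligible: 18 × 18 = 324.
- Eligible: integral of a from 0 to 18 = 162.
- Share never eligible: 324/486 = 67%.
- Head count: 18/36 = 50%.

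**If eligibility in Côte d'Ivoire ran to 24 months** while the rebound period still started at 18, the share is (12 × 18)/486 = 216/486 = 44%. If both ages were 24 months, the Cameroon figure of 57% applies.

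**Sensitivity of the person-time share**

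| Scenario | Cameroon | Côte d'Ivoire |
|---|---|---|
| Base case | 57% | 67% |
| 20% loss over 18 months | 58% | 67–68% |
| PMC starts 3 months after the census | 70% | 77% |
| Age distribution thinning 2% per month | 51% | 60% |

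Births during the study change nothing, because none of these children reaches 18 months of age before it ends.

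**Dilution.** With equal background rates, apparent rate ratio = 1 + (true − 1) × eligible share. For a true value of 1.20:
- Cameroon: 1 + 0.20 × 162/378 = 1.086.
- Côte d'Ivoire: 1 + 0.20 × 162/486 = 1.067, or 1 + 0.20 × 270/486 = 1.111 under the 44% reading.

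**Active cohort.** Age at the last visit is 24 to 27 months in Cameroon (6 + 18 to 9 + 18) and 20.3 to 24 months in Côte d'Ivoire (2.3 + 18 to 6 + 18). Every child was below the cut-off at recruitment, so the never-eligible share is 0%.

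**The case against.** The strongest reply has five parts.

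- **The Study design bands only describe what the census should characterise.** Actual eligibility is set dose by dose in the overview of the intervention, and the schedule is in Fig. 1, which is not shown. This stands in part: the end of the Ivorian schedule is known here only from Data analysis, so one cannot say which section is right. The two ages still conflict.
- **Only children who were once eligible can age out, so the authors surely did not mean to pool the others, and an analysis plan would settle it.** That may be the intent. But residence defines exposure, person-time starts at recruitment, age censoring is ruled out and the period is fixed by age. Applied literally, these stated rules include the never-eligible children. This is a stated rule, not a silence.
- **The active cohort was built to observe ageing out.** This stands, and that cohort is free of the problem. However, cases are taken from either cohort, and nothing confines the rebound estimate to the active one.
- **The share is a majority only in person-time and under an assumed age distribution.** This stands. By head count it is 40% and 50%.
- **Rebound is not a listed objective.** This also stands, and it limits the weight of the point.

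A reader might go further and infer that the 24 to 36 month internal control is wrong or biased. The article does not support that. Children of that age are past the stated limit in both countries. Leaving out Ivorian children aged 18 to 24 months would, if the 18-month age holds, drop 6 of 18 months of baseline age. That costs precision, but no bias has been shown.

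**Conclusion.** The point holds in a limited form. The eligible band under Study design and the Ivorian start of the post-intervention period under Data analysis do not agree and must be reconciled. Separately, the age-only definition lets children with no access to the differing doses into the rebound estimate for the passive or combined cohort.

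Under uniform ages and no loss they supply about 57% of that person-time in Cameroon and 67% in Côte d'Ivoire. The Ivorian figure is conditional on the 18-month age and becomes 44% if eligibility ran to 24 months with the rebound start unchanged. The fall of a true rate ratio of 1.20 to about 1.09 and 1.07 also needs equal background rates in the two groups, which is an assumption because their ages differ.

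The documents do not support extending this to the active cohort or to the primary comparison of malaria incidence between areas. They also do not show which age limit is the correct one.

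**What to change.** 1. Reconcile the age limits in Study design, Passive cohort and Data analysis with each country's dose schedule, and state them by country.
2. Using each country's reconciled last-dose age and date of birth at PMC start, count rebound person-time only for children who were age-eligible, after PMC start, for at least one dose that differs between areas. Apply the same rule in intervention and control areas, whatever doses were actually received.
3. Analyse children already past that age at PMC start separately, as the internal control.

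This takes a few sentences and one variable derived from date of birth, with no new data. The cost is precision. On the ages now stated under Data analysis, the rebound analysis keeps 162/378 = 43% of its person-time in Cameroon and 162/486 = 33% in Côte d'Ivoire. If events are proportional to person-time and clustering is ignored, standard errors grow by √(378/162) = 1.53 and √(486/162) = 1.73.

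The undiluted effect grows by more. For a true rate ratio of 1.20, ln 1.20 / ln 1.086 is about 2.2 and ln 1.20 / ln 1.067 is about 2.8. On these assumptions the restriction costs no power to detect a rebound, although the interval is wider.

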### Sample size

For the passive cohort, we will monitor all eligible children enrolled in the study and will therefore, will constitute a population sample. For the active cohort, the sample size was calculated to ensure 80% power at the 5% significance level, assuming an intra-cluster correlation coefficient of 0.25, and accounting for a 3:1 sampling ratio of intervention to control to ensure sufficient power to assess any variation in PMC effectiveness according to distance to the EPI facility. However, the specific sample size for the number of EPI facilities and children to include in the active cohort was calculated separately for each study site to account for the differences in PMC implementation (Fig. 1).

In Cameroon, we expect a 30% reduction in malaria incidence in intervention compared to control areas, requiring 26 intervention and 9 control EPI facilities are required. With a 20% expected loss to follow-up rate, we require 1,560 in the intervention and 540 children in the control area over the 18 months of observation in the active cohort. In Côte d’Ivoire, the standard of care currently being implemented by the NMP is no doses, so the difference between in the number of SP contacts between arms is 5. Therefore, we expect a 40% reduction in malaria incidence in intervention compared to control areas. Accordingly, 14 and 5 EPI facilities will be required in the intervention and control areas, respectively. Assuming a conservative loss to follow-up rate of 20%, we require 1,148 and 410 children in the intervention and control areas, respectively, over the 18 months of observation in the active cohort.

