Where there are repeated measures per child, random effects or generalising estimating equations models will be used to adjust for non-independence of the data from the same individual. Regression models will assess factors associated with incidence of malaria infection including demographic variables, malaria history, reported vector control use, socio economic position, amongst others [17]. Transmission intensity, type of PMC delivery mode, impact of the estimated protective window of SP, and other factors will be adjusted for to assess their impact on the incidence trends [18]. Subgroup analysis will constitute assessing the impact of distance to the health facility as a proxy for access to health services according to the study endpoints highlighted above. Distance will be assessed according to tertials of distance of all study participants to their nearest health facility and as a continuous variable. Alternate model forms including interaction terms as well as semiparametric approaches to account for time-varying intervention effects to account for the expected 4-week prophylactic period of SP will be tested [19]. Because of the challenges in confirming cause of death in those who die in the community and the assumption that severe malaria cases will seek care at a health facility, only the passive cohort data will be used to assess these secondary outcomes [20]. An interim analysis will be conducted after the 4th active cohort visit and the study will be reported according to the ‘Strengthening the reporting of observational studies in epidemiology’ (STROBE) guidelines [21].

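### Passive case capture names no route for visits to undrawn EPI facilities, and the drawn share differs by arm in opposite directions in the two countries, so passive-cohort rate ratios can be biased

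*Protocol article*

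**What the plan says.** Under Passive cohort, clinical information is collected when an enrolled child "visits a study health facility or CHW, information about their visit will be recorded including date, diagnosis and treatment received". Study design says that EPI facilities are drawn at random and adds one further source: "All non-EPI/PMC facilities within the selected EPI catchment areas, will be included in the passive cohort data collection". The same Passive cohort section speaks of collecting every clinical malaria and anaemia episode, and says caregivers will be encouraged to use participating facilities or CHWs.

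The facility counts come from three sections:
- Cameroon, intervention (Soa): "Of the 39 facilities, 20 administer EPI services".
- Cameroon, control (Mbankomo): "Of the 32 facilities, 19 administer EPI services".
- Côte d'Ivoire, intervention (Séguéla): "Of the 42 facilities, 41 administer EPI services". In the control area (Kani) all 8 do.
- Sample size, Côte d'Ivoire: "14 and 5 EPI facilities will be required in the intervention and control areas, respectively". For Cameroon it asks for 26 intervention and 9 control.

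Data analysis counts confirmed malaria from either cohort and runs person-time from recruitment to censoring or study end. For severe malaria and death it relies on "the assumption that severe malaria cases will seek care at a health facility, only the passive cohort data will be used".

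**The concern.** Two features meet. First, visits to an undrawn EPI facility have no stated way into the individual-level passive data. The routine facility series will not fill the gap, because it is monthly aggregates that cannot be linked to children. Being treated elsewhere does not stop a child's person-time, so each missed case lowers that arm's rate.

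Second, the chance that another EPI facility in the district is a study facility depends on how many were drawn, and that share is far from equal between arms. It is lower in the intervention arm in Côte d'Ivoire and lower in the control arm in Cameroon. If children seek care elsewhere equally often in both arms, the loss is still unequal. It would tend to enlarge the apparent effect in one country and shrink it in the other. The article plans to pool the countries and to compare them, so opposite errors could create or hide a between-country difference.

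**Working it through.** **Facility counts, reproduced first.** I used the standard cluster formula for rates with 3:1 allocation:

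c_control = (1.96 + 0.842)² × [(λ0/y + k²λ0²) + (λ1/y + k²λ1²)/3] / (λ0 − λ1)²

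Here y = children per facility × 0.8 × 1.5 years, and the stated 0.25 is read as a between-cluster coefficient of variation k.
- Cameroon: λ0 = 0.597, λ1 = 0.70 × 0.597 = 0.418, 540/9 = 60 children per facility, y = 72. Result: 8.84 control and 26.5 intervention (stated 9 and 26).
- Côte d'Ivoire: λ0 = 0.572, λ1 = 0.60 × 0.572 = 0.343, 410/5 = 82 children per facility, y = 98.4. Result: 4.48 and 13.4 (stated 5 and 14).

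So 26 is what the calculation yields, not a slip of the pen, yet Soa has only 20 EPI facilities. I cap Soa at 20/20.

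**Drawn share f**

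| | Intervention | Control |
|---|---|---|
| Côte d'Ivoire | 14/41 = 0.341 | 5/8 = 0.625 |
| Cameroon | at most 20/20 = 1 (26/20 = 1.30 is impossible) | 9/19 = 0.474 |

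**What the non-EPI facilities add.** In Côte d'Ivoire, almost nothing: 42 − 41 = 1 in Séguéla and 0 in Kani. In Cameroon there are 39 − 20 = 19 in Soa and 32 − 19 = 13 in Mbankomo, but only those in drawn catchments count, so they follow the same imbalance.

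**Effect on the rate ratio.** Let s be the share of case visits made to another EPI facility in the district. This is an assumption; the article gives no figure. I take s as equal in both arms, with visits spread evenly over the district's EPI facilities. Captured share = 1 − s(1 − f), so

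observed RR = true RR × [1 − s(1 − f_int)] / [1 − s(1 − f_ctl)]

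| s | Côte d'Ivoire, true RR 0.60 | Cameroon, true RR 0.70 |
|---|---|---|
| 0 | 0.60 (40%) | 0.70 (30%) |
| 10% | 0.60 × 0.934/0.963 = 0.582 (42%) | 0.70 × 1/0.947 = 0.739 (26%) |
| 20% | 0.60 × 0.868/0.925 = 0.563 (44%) | 0.70 × 1/0.895 = 0.782 (22%) |
| 30% | 0.60 × 0.802/0.887 = 0.542 (46%) | 0.70 × 1/0.842 = 0.831 (17%) |

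Percentages in brackets are the apparent reductions, for passive capture alone.

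**Two checks.**
- A child's own facility is drawn by construction, so the share among the others is (drawn − 1)/(total − 1): 13/40 = 0.325 against 4/7 = 0.571, and 19/19 = 1 against 8/18 = 0.444. At s = 20% this gives 0.60 × 0.865/0.914 = 0.568 (43%) and 0.70 × 1/0.889 = 0.788 (21%). Little changes.
- In Cameroon the direction holds only if more than 20 × 9/19 = 9.5 of Soa's 20 facilities are drawn.

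**The case against.** The strongest reply has five parts.

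- **Capture is wider than the drawn facilities.** A reader might infer that cases are recorded only at the randomly selected facilities. The article does not support that. CHWs and non-EPI facilities in drawn catchments report too, and active-cohort children are tested at home every three months and asked about diagnoses and where care was sought. This stands. But the questionnaire reaches only the active cohort, no rule says that a recalled outside diagnosis is confirmed and counted, and outcomes taken from passive data alone gain nothing from it.
- **The 30% and 40% effects are set for the active cohort.** This stands. The table applies them to passive capture for illustration and does not forecast the error in the combined malaria incidence.
- **The design has internal controls.** Children aged 24 to 36 months in the same catchments, and the difference-in-difference models, would offset leakage that is similar across ages or stable over time. This stands in part: it needs care-seeking elsewhere to be alike at both ages, and the article also plans direct area-to-area rate ratios.
- **s is unknown and may be small.** Caregivers are steered to participating facilities, and in a rural district distance governs choice, so even spread is a crude proxy. Care outside the district is not modelled. This stands, and it is why the bias is possible rather than shown.
- **Which registers are read is operational detail.** A reader might infer that the referral hospital is left out. Nothing says so: hospital deaths and inpatient details are to be collected, and health IDs support linkage. A condensed article may leave the list of hospitals to the full protocol. But the article does fix where visits are recorded, and it leaves undrawn EPI facilities out.

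**Conclusion.** The concern holds as a risk of differential ascertainment, not as a demonstrated bias. The rule for recording visits gives no route for undrawn EPI facilities. The drawn shares are 34% against 63% in Côte d'Ivoire and at most 100% against 47% in Cameroon. If enrolled children use other EPI facilities, passive-cohort rate ratios would tend to overstate the effect in Côte d'Ivoire and understate it in Cameroon.

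The distortion is nil at s = 0 and modest at s = 10% (2 and 4 percentage points). At s = 30% it reaches about 6 and 13 points. These sizes assume equal s in both arms, even spread over the district and no active detection. Active testing, the follow-up questionnaire and the older-child control reduce the problem without removing it. Severe malaria and malaria deaths are most exposed because they use passive data alone; their error cannot be sized from the article.

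The Cameroon figures are conditional on a count that the article contradicts: the 26 required and the 20 available must be reconciled before that share means anything. The figure that sets out facility numbers by component is not available in the text reviewed and may bear on this.

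**What to change.** 1. At the 3-monthly census updates already planned, abstract from each enrolled child's record book any RDT- or microscopy-confirmed malaria, any anaemia diagnosis and any admission at any facility since the last visit. State that these count as cases.
2. Name the inpatient and referral units serving both arms as data sources for severe outcomes, whether or not they are drawn.
3. Report effects with and without cases from non-study facilities, by country. The outside-case counts by arm also show how much care-seeking leaks and whether it differs.
4. Reconcile the Cameroon intervention facility count between Sample size and the Cameroon site description.

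The cost is a few eCRF fields at visits already made, plus extraction from a small number of inpatient registers. Visits become slightly longer, and the result depends on how completely record books are filled in, which may itself vary by facility.
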